#### Content Delivery Forms

The content of the Untire app is presented in different forms. Patients and survivors of cancer can read educative articles, but often also an audio option is available, as listening to the material instead of reading it might be less tiring for patients with CRF. Besides reading texts and listening to audio texts or exercises, the Untire app contains numerous video animations aimed to explain complex aspects and exercises in an easy to understand and visually attractive way. Apart from the form of content delivery (ie, text, audio, and video), also persuasive elements (eg, motivational pictures in between blocks of text) are used to visualize key aspects (eg, the biological clock for sleeping quality). Other persuasive elements include progression bars, rewards, badges, and constant encouragements. To encourage participants to use the app at their own pace, they receive gentle reminders to take a break after going through 5 pages within a theme. The app fosters social commitment by supporting participants to invite a so-called *buddy*. In this way, participants can manage their fatigue together with a family member or friend. Furthermore, participants are also invited to join the Untire community on Facebook, which provides a platform for the exchange of thoughts and allows socializing in a broader social environment.

#### App Version

The study used version 2.1 of the app, which has been developed based on a pilot and feasibility study with version 1.0, and a usability study with 19 users and 9 professionals focusing on the content, use, and technical aspects of version 2.0. For version 2.1, improvements were made in the onboarding system, tone-of-voice, and presentation of content. For the improvements in the onboarding system, an additional 5 users participated in a UX usability test. During the study, only minor technical updates and changes (ie, mostly bug fixes) have been made.

### Outcome Assessment

Data in this study have been collected by means of Web-based questionnaires and in-app log data. Table 2 presents a complete overview of the variables assessed by the Web-based questionnaires at each measurement wave for the intervention and control participants, respectively. Variables were assessed by either using validated questionnaires, using a selection of items of a validated questionnaire, or by items specifically created for this trial. We realize it may be a burden for patients with CRF to fill out all these assessments. To enhance patients’ commitment to the study and to reduce attrition, we carefully selected a limited number of questionnaires and items to include.

**Table 2 table2:** Questionnaires to assess the primary outcome, secondary outcomes, moderators, mediators, and explanatory factors (including background attitudes, experiences of app use, and cost-effectiveness).

Variables				Measurement (number of items)	Measurement in weeks					
					0 (baseline)	4	8	12		24
**Primary outcome measure**										
	Fatigue symptoms			FSI^a^ (15): Severity Scale (4) and Interference Scale (7)	I^b^C^c^	IC	IC	IC	IC	
**Secondary outcome measures**										
	QoL^d^			EORTC-QLQ-30^e^—Past week (1) and QoL—On Average (1)	IC	IC	IC	IC		IC
**Moderators**										
	Demographic and health characteristics			—^f^	IC	—	—	—		—
**Mediators**										
	Mindfulness			MAAS-5^g^ (5)	IC	IC	IC	IC		IC
	Physical activity			(3)	IC	IC	IC	IC		IC
	Depression			PROMIS-29^h^ (4)	IC	IC	IC	IC		IC
	**Sleep**									
		Quality		PROMIS-29 (1)	IC	IC	IC	IC		IC
		Disturbance		SLC-90-R^i^ (3)	IC	IC	IC	IC		IC
	Fatigue catastrophizing			FCS^j^ (13): Rumination (4), Magnification (3), and Helplessness (6)	IC	IC	IC	IC		IC
**Explanatory factors**										
	Patients expectancy			(3)	I	—	—	C		—
	Patients motivation			(2)	I	—	—	C		—
	Patients support in environment			WHYMPI/MPI^k^ (5)	IC	IC	IC	IC		IC
	Pain interference			RAND-36^l^ (2)	IC	IC	IC	IC		IC
	Experienced changes			(5)	—	—		IC		IC
	User experience of the app			(19)	—	—	—	I		C
	Cost-effectiveness			(6)	—	—	—	IC		—

^a^FSI: Fatigue Symptom Inventory (fatigue severity scale, fatigue interference scale).

^b^I: intervention measurement.

^c^C: control measurement.

^d^QoL: quality of Life.

^e^EORTC-QLQ-30: European Organization for Research and Treatment for Cancer Quality of Life Questionnaire.

^f^Not applicable.

^g^MAAS-5: The Mindful Attention Awareness Scale.

^h^PROMIS-29: Patient-Reported Outcomes Measurement Information System (depression scale, sleep scale).

^i^SLC-90-R: Symptom Checklist-90-Revised (sleep disturbance scale).

^j^FCS: Fatigue Catastrophizing Scale (fatigue catastrophizing—adapted from PCS: Pain Catastrophizing Scale; rumination, magnification, and helplessness scales).

^k^WHYMPI/MPI: The West Haven-Yale Multidimensional Pain Inventory.

^l^RAND-36: Research and Development (pain interference scale).

#### Primary Outcome Measure

The primary outcome is the change of fatigue severity and fatigue interference from baseline to 12 weeks, which was assessed with the self-report questionnaire FSI [20,21]. Fatigue severity was assessed by calculating the average of 3 severity items (FSI items 1-3: *Rate your average level of fatigue during the past week; Rate your level of fatigue on the day you felt most fatigued during the past week; Rate your level of fatigue on the day you felt least fatigued during the past week*) on an 11-point Likert-scale ranging from 0 (not at all fatigued/no interference) to 10 (as fatigued as I could be/extreme interference). Fatigue interference was assessed by calculating a composite score of the average of 7 interference items (FSI items 5-11: *Rate how much, in the past week, fatigue interfered with your general level of activity, ability to bathe and dress, normal work activity [includes both work outside the home and housework, ability to concentrate, relations with other people, enjoyment of life, mood]*). A higher score indicates stronger severity or interference.

#### Secondary Outcome Measures

The secondary outcome is change in QoL from baseline to 12 weeks, which was assessed with the 1-item European Organization for Research and Treatment of Cancer Quality of Life Questionnaire (*How would you rate your overall quality of life during the past week?* [28]) as well as a self-constructed item of overall QoL (Overall QoL: *How would you rate your overall quality of life on average?*) on a 7-point Likert-scale ranging from 0 (very poor) to 7 (excellent). A higher score indicates a better QoL.

#### Moderating Factors

Demographic data were gathered on age, gender, country of residence, level of education, employment status, relationship status, and illness-related characteristics, such as being a patient or survivor of cancer, time since diagnosis, and type of treatment received.

#### Mediating Factors

The following potential mediating factors were assessed: mindfulness, physical activity, depression, sleep, and fatigue catastrophizing. Mindfulness was measured with the Mindful Attention Awareness Scale [29]. To measure physical activity, we constructed 3 questions regarding engagement in light, moderate, and vigorous physical activities. Depression was measured with the depression subscale of the Patient-Reported Outcomes Measurement Information System (PROMIS-29) [30]. Sleep was measured with the 1-item sleep quality subscale of the PROMIS-29, and 3 items of the sleep disruption subscale of the Symptom Checklist-90-Revised [31]. The fatigue catastrophizing scale was adapted from the Pain Catastrophizing Scale [32], and measured by the rumination, magnification, and helplessness subscales.

#### Explanatory Factors

Explanatory factors were included as these were assumed to be potentially helpful for the interpretation of the study results. Patients’ attitudes were assessed with questions about their expectations, motivations, and experienced support in their environment. Furthermore, as a proxy of impaired physical functioning, pain interference was assessed. Pain interference was measured with 2 items of the Research and Development Health Survey [33]. Perceived changes in levels of fatigue, overall QoL, physical activity, mood, and sleep were assessed with 1-item questions. User experience with the app was assessed to explore patients’ attitudes toward and experiences with the Untire app. Cost-effectiveness was assessed to explore the costs and benefits of the Untire app (see Table 1).

#### In-App Log Data

Log data are used to explore the characteristics of app use. Once participants activated their unique access code and gave consent to the privacy terms in the Untire app, participants were registered, and their log data were stored anonymously. Log data are automatically stored data about the activities and assessments (ie, Quick scans and the Vase of Energy) that participants perform, and registers the date on which activities and assessments were performed. App use can be described based on (1) the duration of app use in days and (2) the degree of app use. Log data will indicate the first, and the last time a participant completed an activity and the number of days between the first and last activity will be used as a proxy for the duration of app use. The number of completed activities will be counted and will be used as a proxy for the degree of app use, with a higher number of completed activities indicating more app use.

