### Intervention

Participants in the intervention group were instructed to work through the app at their own pace and could freely choose modules to work on. Although daily use of the Untire self-management app was recommended, participants were instructed to use the app at least once a week. Users who had not been active for 5 days were sent a reminder. Users who opened the app at least seven times within 10 days received a rating pop-up (ie, to assess satisfaction and ask for feedback).

After opening the Untire app for the first time, participants received a short introduction on how to use the app. Participants were informed that every time they revisit the app (ie, reopen the app), a (new) daily program will be presented. The daily program consists of the 4 following core components: (1) *My themes*, (2) *My exercises*, (3) *Tip of the day*, and (4) *My physical activity* (Figure 2). Participants also received information about the weekly assessments of their fatigue and related components, the so-called *Quick scan*. The *Vase of Energy* is an integral part of the Quick scan. Participants were also invited to think about informing a friend or family member, a so-called *buddy*, to help or motivate them to work with the app. All the modules are explained below in detail (also see Table 1 and Figure 2).

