### Main Analyses

#### Does the Untire App Reduce Fatigue Significantly After 12 Weeks of App Access?

To examine a treatment effect of the app on fatigue, the data collected via Questback’s Web-based survey of fatigue severity and interference will be analyzed using General Linear Mixed Models (GLMM) for 4 repeated measures (baseline, 4 weeks, 8 weeks, and 12 weeks), and 2 groups (intervention and control), following the intention-to-treat (ITT) approach. The ITT approach refers to analyzing all participants, regardless of app use, and is the primary approach in all outcome analyses. Assumptions of linearity, homogeneity of variance as well as the normal distribution of residuals of the model will be tested. The individual measures of fatigue ratings over time (level 1) are nested within each patient (level 2). The default GLMM model without a country factor will be compared with a model with a country factor concerning the best model fit using the Bayesian information criterion.

On the basis of previous studies testing health-related apps targeting behavior [34-39], we estimated the percentage of participants that would lose interest in the app or study assessments, and, therefore, would be lost to follow-up (eg, the 12-weeks measurement), at 60%. For the data analysis, we will, therefore, employ a model that can take missing data into account (ie, GLMM). A comparison of the outcomes of the model run in the ITT approach and the outcomes of a model run among those who have completed at least the 12-week assessment (T12-completers) will demonstrate the robustness of the findings.

In addition to the model validation, we will carry out sensitivity analyses to determine whether the duration and the degree of app use are related to the degree of change in fatigue severity and interference over time. Outcomes of active users will be compared with less-active users. Active and less-active users are categorized according to the duration and degree of app use. The dose-response relationship of app use and treatment effects will be explored in a three-way interaction (time×group×activity level), using GLMM.

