#### What Are the Reach, Costs of Online Recruitment, and What Is the Uptake and Usage of the Untire App (Study)?

To explore the number of participants reached using Web-based social media campaigns, we will use the number of Web-based advertisement link clicks, leading to the study landing page. To determine the costs of recruitment, the number of link clicks will be compared with the budget spent on social media campaigns. We will calculate the total costs of recruitment, the costs per person who clicked the link, and the costs per person that completed the baseline (study) assessment. To examine how many participants completed the assessments, activated the app, and used the app in the first 12 weeks of the study, percentages and count data will be used. Log data will indicate how many participants activated their unique access code, the number of days a participant has been active in the app, and the number of activities performed.

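### Duration of app use is a first-to-last calendar span, and neither it nor the activity count is stopped at week 12, leaving the exploratory dose-response analysis open to misclassification and reverse causation

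*Protocol article*

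**What the plan says.** Four places in the protocol article bear on this.

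- **In-App Log Data** sets two measures of use. For duration, "the number of days between the first and last activity will be used as a proxy for the duration of app use". For degree, "The number of completed activities will be counted and will be used as a proxy for the degree of app use". Neither has an end date. The same section says that the log "registers the date on which activities and assessments were performed".
- **Main Analyses** (fatigue after 12 weeks) puts both to work: "Active and less-active users are categorized according to the duration and degree of app use". It continues: "The dose-response relationship of app use and treatment effects will be explored in a three-way interaction (time×group×activity level), using GLMM". This is introduced as a sensitivity analysis. No cut-point is given, no rule for combining the two measures, and no window for the log data.
- **Primary Outcome Measure** fixes the time point that use is meant to explain: "The primary outcome is the change of fatigue severity and fatigue interference from baseline to 12 weeks".
- **Secondary Analyses**, on reach, recruitment costs, uptake and usage, describes the same logs differently. They will show "the number of days a participant has been active in the app, and the number of activities performed", and the sentence before places app use in the first 12 weeks.

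Nothing in the document ends intervention participants' access at week 12. Study Design and Setting says that the app could still be had after recruitment closed and that controls received a year of free access after 12 weeks. Follow-up ran to week 24.

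**The concern.** A first-to-last span measures how long someone went before the final contact with the app. It ignores what happened in between, so a person who opened the app twice can score as longer exposed than one who used it every day for a month.

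The missing end date matters more. Use after week 12 cannot have caused the week-12 fatigue score, but the week-12 score may well influence whether someone carries on. If later use enters the exposure, people who felt better and stayed with the app are scored as having had more of it, and an association read as dose-response could run from outcome to use.

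At stake is the reading of the app-use results. Usage is among the secondary aims, and Randomization and Blinding gives in-depth app-use analysis as one of two reasons for 2:1 allocation. The sections also disagree: reported duration would depend on which one the analyst follows.

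**Working it through.** The plan attaches no figure to these measures, so there is none to reproduce. The check applies the stated definitions to simple usage logs. The logs are assumed, with one activity per active day and days counted from randomisation.

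Formulas:

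- Span = day of last activity − day of first activity (In-App Log Data).
- Count = number of completed activities (In-App Log Data).
- Active days = distinct days with at least one activity, up to day 12 × 7 = 84.

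| Log | Days with an activity | Span, no cut | Count, no cut | Active days to day 84 | Count to day 84 |
|---|---|---|---|---|---|
| A | 1 and 84 only | 84 − 1 = 83 | 2 | 2 | 2 |
| B | daily, 1 to 28 | 28 − 1 = 27 | 28 | 28 | 28 |
| C | daily, 1 to 7, then 168 | 168 − 1 = 167 | 8 | 7 | 7 |
| D | weekly, 1 to 78 | 78 − 1 = 77 | 12 | 12 | 12 |
| E | weekly, 80 to 157 | 157 − 80 = 77 | 12 | 1 | 1 |
| F (control) | daily, 85 to 112 | 112 − 85 = 27 | 28 | 0 | 0 |

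**Sparse use (A against B).** The span gives A about three times the duration of B (83/27 = 3.1). The count reverses this (2 against 28). The second measure therefore corrects the order here, although the duration component on its own is misleading.

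**One late activity (C).** A single activity on day 168 lifts the span from 7 − 1 = 6 days to 167. The count moves only from 7 to 8.

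**Use after the outcome (D against E, and B against F).** D and E are identical on both stated measures (77 days, 12 activities), but D has 12 active days before the outcome and E has 1. B and F are also identical (27 days, 28 activities), yet F is a control whose use lies wholly after week 12. No combination of the two uncut measures can separate these pairs. A cut at week 12 does.

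**How often could late use arise?** The documents give no usage data, so this rests on an assumption. If engagement starts at randomisation and its length is exponential with mean m days, the share still engaged after day 84 is exp(−84/m):

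- m = 28: exp(−3.0) = 5%
- m = 60: exp(−1.4) = 25%
- m = 120: exp(−0.7) = 50%

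These slightly overstate the share with a logged activity after day 84, because the last activity falls at or before the end of engagement. Strengths and Limitations expects high drop-out and sparing use, which points towards the lower part of the range.

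**The case against.** The best reply is that the span is labelled a proxy for duration only. Intensity has its own measure, the activity count, and the classification uses both. That stands: a reader might infer that the span is the whole dose, and the text does not say so. On logs A and B the count puts the two users in the right order.

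A reader might also infer that the active/less-active split is wrong. The documents do not support that either. Without a cut-point or combination rule, the split is open to misclassification but cannot be shown to misclassify any given share of users. A simulated split on span alone would test a rule that the plan does not contain.

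On the window, one can say that the fatigue model covers only baseline to week 12, that the usage section names the first 12 weeks, and that extraction dates for log data belong in an analysis plan. This has some force: the document as a whole is not without a 12-week limit. But the limit sits in the descriptive usage question, while the definitions that feed the fatigue analysis are written out without it. It can also be said that a descriptive count of active days may coexist with a duration measure, or is a loose restatement of it. Either reading is possible, and the text does not settle which applies.

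Two further inferences go beyond the text. Nothing says that participants who never activated the app are dropped. Logs begin at activation and the scoring of non-activators is not stated, so their loss is a risk and not a rule. And although "participants were instructed to use the app at least once a week", the plan never promises to test adherence against that instruction, so it need not define an active user.

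**Conclusion.** The point holds in a limited form. The stated duration measure can score sparse use as long use, and both stated measures can include use after the week-12 outcome. The activity count offsets the first problem and does nothing for the second. The usage section describes the same logs by another measure and with a window, so the sections need reconciling.

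In the examples, the span differs from active days by 83 against 2, and 11 of 12 counted activities can fall after day 84. How many participants are affected is unknown. The share with late use could run from about 5% to 50% under the assumed engagement lengths.

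The affected analysis is exploratory. The primary intention-to-treat comparison does not use the log data and is untouched. This is a cheap improvement and not a threat to the trial's main result.

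**What to change.** In In-App Log Data and in the app-use paragraph of Main Analyses:

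1. Take the number of distinct active days as the duration measure, in line with the usage section.
2. Restrict it and the count of completed activities to the time from randomisation to the participant's week-12 assessment, or to day 84 if that assessment was missed.
3. Score intervention participants who never activated the app as zero use and keep them in the comparison.
4. Report the first-to-last span descriptively only.

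The cost is analysis wording. Activities are dated in the log, active days are already planned for the usage section, and the link between logs and survey data is one that the planned analysis needs anyway. The downsides are that reported exposure will look lower and that time in engagement becomes a descriptive quantity.

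Two limits remain. The window removes use after the outcome but does not make the comparison of active with less-active users a randomised one, and fatigue at weeks 4 and 8 can still influence later use within the window. Also, controls will by design score zero up to week 12, so the plan should say what activity level means in that arm.

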#### Data Management

Data collection took place over the internet on the secured and password-encrypted server of Questback. Anonymous back-ups were saved on the secured and encrypted server of the UMCG, permitting only access to the involved researchers.

### Statistical Analyses

#### Preparatory Analyses

We will present baseline characteristics (ie, demographics, disease, and treatment characteristics) for each variable side by side for the intervention and control groups by the mean (standard deviation), or frequencies and percentages.

### Main Analyses

#### Does the Untire App Reduce Fatigue Significantly After 12 Weeks of App Access?

To examine a treatment effect of the app on fatigue, the data collected via Questback’s Web-based survey of fatigue severity and interference will be analyzed using General Linear Mixed Models (GLMM) for 4 repeated measures (baseline, 4 weeks, 8 weeks, and 12 weeks), and 2 groups (intervention and control), following the intention-to-treat (ITT) approach. The ITT approach refers to analyzing all participants, regardless of app use, and is the primary approach in all outcome analyses. Assumptions of linearity, homogeneity of variance as well as the normal distribution of residuals of the model will be tested. The individual measures of fatigue ratings over time (level 1) are nested within each patient (level 2). The default GLMM model without a country factor will be compared with a model with a country factor concerning the best model fit using the Bayesian information criterion.

On the basis of previous studies testing health-related apps targeting behavior [34-39], we estimated the percentage of participants that would lose interest in the app or study assessments, and, therefore, would be lost to follow-up (eg, the 12-weeks measurement), at 60%. For the data analysis, we will, therefore, employ a model that can take missing data into account (ie, GLMM). A comparison of the outcomes of the model run in the ITT approach and the outcomes of a model run among those who have completed at least the 12-week assessment (T12-completers) will demonstrate the robustness of the findings.

In addition to the model validation, we will carry out sensitivity analyses to determine whether the duration and the degree of app use are related to the degree of change in fatigue severity and interference over time. Outcomes of active users will be compared with less-active users. Active and less-active users are categorized according to the duration and degree of app use. The dose-response relationship of app use and treatment effects will be explored in a three-way interaction (time×group×activity level), using GLMM.

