**Methods:**

The Untire app study is a waiting list RCT targeting cancer patients and survivors who experience moderate to severe fatigue via social media (Facebook and Instagram) across 4 English-speaking countries (Australia, Canada, the United Kingdom, and the United States). The Untire app includes psychoeducation and exercises concerning energy conservation, activity management, optimizing restful sleep, mindfulness-based stress reduction, psychosocial support, cognitive behavioral therapy, and physical activity. After randomization, participants in the intervention group could access the Untire app immediately, whereas control participants had no access to the Untire app until the primary follow-up assessment at 12 weeks. Participants completed questionnaires at baseline before randomization and after 4, 8, 12, and 24 weeks. The study outcomes are fatigue (primary) and quality of life (QoL; secondary). Potential moderators and mediators of the hypothesized treatment effect on levels of fatigue and QoL were also assessed. Link clicks and app activation are used to assess reach and uptake, respectively. Log data are used to explore the characteristics of app use. Sample size calculations for the primary outcome showed that we needed to include 164 participants with complete 12-week measures both in the intervention and the control groups. The intention-to-treat approach is used in the primary analyses, which refers to analyzing all participants regardless of their app use.

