### Sample Size

Sample size calculations for the primary outcome of fatigue showed that we needed to include 164 participants with complete 12-weeks measures in the intervention and the control group (total N=328) to detect a between-group difference in change from baseline to 12 weeks with a minimal effect size of η^2^=0.10 (alpha=.05, 1−beta=.95). The sample size was calculated using the simplest between/within-group comparison (F tests—repeated measures analysis of variance [with within-between interaction]) in G*Power 3.1. With the inclusion of 820 participants (410 intervention participants; 410 control participants) and an estimated drop-out of (492/820) 60.0%, 164 participants are expected to remain in the intervention and 164 in the control group at the 12-week primary outcome measurement. The total baseline completer sample size of N=820 can be taken as a conservative upper bound as the final analyzes will be carried out using GLMM. GLMM takes more information into account and, thus, requires a smaller sample size given the same power.

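### The primary mixed model reads as leaving the baseline group difference free; a common baseline mean would give a modest gain in precision at almost no cost

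*Protocol article*

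**What the plan says.** - **Primary model** (protocol article, Main Analyses): a mixed model "for 4 repeated measures (baseline, 4 weeks, 8 weeks, and 12 weeks), and 2 groups (intervention and control". The structure given is "The individual measures of fatigue ratings over time (level 1) are nested within each patient (level 2". The fixed effects are not written out, and neither a baseline covariate nor a constraint on the baseline means is mentioned.
- **Endpoint** (Primary Outcome Measure): "The primary outcome is the change of fatigue severity and fatigue interference from baseline to 12 weeks".
- **Powered contrast** (Sample Size): "to detect a between-group difference in change from baseline to 12 weeks", sized with "F tests—repeated measures analysis of variance [with within-between interaction".
- **Related models**: the dose-response analysis "will be explored in a three-way interaction (time×group×activity level), using GLMM". The moderator analyses have the same three-way form.
- **Timing** (Abstract, Methods): "Participants completed questionnaires at baseline before randomization and after 4, 8, 12, and 24 weeks".
- **QoL** (Secondary Analyses): analysed by the same procedure as fatigue.

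**The concern.** In a group-by-time model that includes baseline and leaves every cell mean free, the week-12 treatment effect is the week-12 group difference minus the baseline group difference. Because baseline was measured before allocation, the true baseline difference is zero by design. Estimating it spends information on a known quantity and carries part of any chance imbalance into the result. A model that gives both arms one baseline mean targets the same week-12 effect with a variance that is no larger and usually smaller.

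The stake is precision at week 12, where the article expects only 40% of participants to remain. The same model form is used for both fatigue scales and for QoL.

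**Working it through.** **1. The plan's own figure.** For the interaction F test, the noncentrality is λ = f²·N·m/(1−ρ), with 1 and N−2 degrees of freedom when m = 2. With f = 0.10, m = 2, ρ = 0.5 and alpha 0.05, N = 328 gives power 0.951, so the stated 328 is reproduced, and 328/0.4 = 820. The article states neither m nor ρ. It prints "minimal effect size of η^2^=0.10 (alpha=.05, 1−beta=.95". Read literally, η² = 0.10 means f = 0.333 and gives N = 32, so f = 0.10 is the value that matches 328. That discrepancy is a separate matter and is used here only to fix the design effect. In a 2×2 layout f = δ/(4·SD), so f = 0.10 means a difference in change of δ = 0.4 SD. This calculation is a change-score comparison, in which the baseline difference is free.

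**2. Complete data (the T12-completer analysis).** Per arm of n, with equal variances over time:
- free baseline: 2(1−ρ)·SD²/n
- common baseline mean: (1−ρ²)·SD²/n
- ratio: (1+ρ)/2, which is 0.65, 0.75 and 0.85 at ρ = 0.3, 0.5 and 0.7

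At ρ = 0.5 and 164 per arm, power goes from 0.952 to 0.987.

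**3. Primary model under 60% drop-out, baseline and week 12 only.** All n₀ baselines are kept and n₁ = q·n₀ people reach week 12. Per arm, in SD² units:
- free baseline: (1−ρ²)/n₁ + (1−ρ)²/n₀
- common baseline mean: (1−ρ²)/n₁

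With n₀ = 410, n₁ = 164 and ρ = 0.5:
- free: 0.75/164 + 0.25/410 = 0.004573 + 0.000610 = 0.005183; SE of the contrast √(2 × 0.005183) = 0.1018; power for 0.4 SD is 0.976
- common: 0.004573; SE √(2 × 0.004573) = 0.0956; power 0.987
- variance ratio 0.882

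The general ratio is (1+ρ)/[(1+ρ) + q(1−ρ)]. With q = 0.4 it is 1.3/1.58 = 0.823 at ρ = 0.3 and 1.7/1.82 = 0.934 at ρ = 0.7.

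**4. All four waves.** This uses the generalised least squares information matrix for the week-12 contrast, with and without the baseline group term. Assumptions: monotone retention of 75%, 55% and 40% at weeks 4, 8 and 12, the same in both arms; equal variances; ρ is the baseline to week-12 correlation.

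| ρ | Ratio, compound symmetry | Ratio, decaying correlation | Variance cut |
|---|---|---|---|
| 0.3 | 0.818 | 0.801 | 18-20% |
| 0.5 | 0.875 | 0.861 | 12-14% |
| 0.7 | 0.927 | 0.918 | 7-8% |

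The ratios are the same for 410:410 (Sample Size) and 545:302 (Results). With 545:302, compound symmetry and a similar retention pattern (80/60/40%), power goes from 0.977 to 0.989 at ρ = 0.5, from 0.926 to 0.965 at ρ = 0.3, and stays at 0.999 or above at ρ = 0.7.

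**5. If baseline varies less than follow-up.** Entry requires an average above 3 on FSI items 1-3, the same items that form the severity outcome, so selection may shrink the baseline SD. Let the baseline SD be k times the follow-up SD. The (1−ρ)² term in step 3 becomes (k−ρ)². For k = 0.7 (illustrative) and q = 0.4:
- ρ = 0.3: 0.91/(0.91 + 0.4 × 0.16) = 0.91/0.974 = 0.934, a cut of about 7%
- ρ = 0.5: 0.75/(0.75 + 0.4 × 0.04) = 0.75/0.766 = 0.979, about 2%
- ρ = 0.7: (0.7 − 0.7)² = 0, so no gain

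**The case against.** **The text does not state a free baseline difference.** This stands. A model with baseline as an outcome and one common baseline mean fits the Main Analyses sentence equally well, so placing baseline among the outcomes is not itself the fault. The article is condensed, and a full protocol or SAP may settle the matter. The free-baseline reading remains the likelier one, because the endpoint and the powered contrast are both differences in change, the sizing test is a within-between interaction, and an equality constraint has to be stated to apply. The Sample Size section does call its test the simplest comparison and says the final model will differ, so the reading is still an inference.

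**The planned analysis is valid and well powered.** This also stands. The target was 95% power, and at ρ = 0.5 both models exceed it.

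**The size is uncertain.** The article gives no correlation, no retention by wave and no variance ratio. Selection on the FSI could remove most of the gain for severity; the argument is weaker for interference, which is not the selection score.

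**Two further readings are tempting but unsupported.** A reader might take the 25% reduction at ρ = 0.5 as the loss in the primary analysis. It belongs to the completer analysis, which the article uses as a robustness check. A reader might also think the planned model discards people who have only a baseline. It does not, because baseline is an outcome, and this is why the primary loss is about half the completer figure.

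**Conclusion.** The point holds as a minor matter of efficiency. On its natural reading, the primary model estimates a baseline group difference that randomisation makes zero. A common baseline mean would cut the variance of the week-12 contrast by about 12-14% at ρ = 0.5, within 7-20% over ρ = 0.7 to 0.3, given 60% drop-out, the assumed retention pattern and equal variances. If the baseline SD were 0.7 of the follow-up SD, the gain would be about 0-7%. Power at the design effect moves by about 1 point at ρ = 0.5 and nearly 4 points at ρ = 0.3.

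Nothing here supports a claim that the planned estimate is biased or that its type I error is inflated.

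**What to change.** State the fixed effects of the primary model: one baseline mean common to both arms, and group-by-categorical-time terms at weeks 4, 8 and 12. Report the week-12 group difference from that model. Use the same form for QoL.

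This is preferable to entering baseline as a covariate. A covariate model drops everyone with no follow-up questionnaire (25% of participants under the retention assumed here), which sits badly with an intention-to-treat analysis of all participants.

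No new data are needed. The cost is one of documentation: assessments ended in March 2019 and allocation was not blinded, so the change should be recorded as made after data collection. Keep the unconstrained model as a sensitivity analysis so that readers can see both results. If a full protocol or SAP already fixes a common baseline mean, one clarifying sentence is enough.
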